## Abstract

**Background:**

The current first-line treatment for binge eating disorder (BED), which is psychotherapy, is moderately effective in terms of abstinence from binge-eating. Neurobiological evidence suggests that people affected by BED show difficulties along the spectrum of impulsivity, including inhibitory control impairments and highlights the potential of novel treatment approaches directly targeting inhibitory control, including cognitive training approaches and non-invasive brain stimulation.

**Methods:**

ACCElect is a prospective, randomized controlled pilot trial investigating a novel, food-related inhibitory control training combined with transcranial direct current stimulation (tDCS). 40 patients with BED will be randomly assigned to receive the training either combined with verum or with sham stimulation (control condition). The inhibitory control training is based on principles of the antisaccade paradigm and comprises six training sessions over two weeks. Core aims are the investigation of feasibility and clinically relevant effects of a tDCS-enhanced inhibitory control training in BED patients and the establishment of a data basis for a larger efficacy trial. The primary clinical endpoint is binge-eating (BE) frequency in terms of changes in BE episodes four weeks after treatment termination as compared to baseline. Key secondary outcomes comprise ED pathology and general psychopathology, inhibitory control capacities, quality of life as well as acceptability and satisfaction with the intervention.

**Discussion:**

The results of the present trial will contribute to the development of novel neurobiologically informed treatment approaches for patients suffering from BED.

*Trial registration* The ACCElect trial was prospectively registered on October 1, 2020, under the registration number NCT04572087 at ClinicalTrials.gov **(**https://clinicaltrials.gov/ct2/show/NCT04572087).

## Background

Binge Eating Disorder (BED) is the most common eating disorder (ED) in the general population [1, 2]. Psychotherapy is recommended as the first-line treatment for people with BED [3, 4], while cognitive-behavior therapy (CBT) is currently supported by the largest evidence base [3]. Many patients with BED profit from psychotherapy in terms of central treatment goals such as reduction of or abstinence from binge-eating as core psychopathology of BED, improvements in ED pathology and in quality of life. According to a recent meta-analysis, around half of patients treated with psychotherapy achieve abstinence from binge-eating which is maintained over a 12-months period [5]. However, this also means that the other half of patients still suffer from binge-eating episodes when terminating treatment, hence they do not sufficiently benefit from the first-line treatment.

Given the considerable burden associated with BED [6], these numbers highlight the need for improved therapy outcomes which might be achieved by novel treatment approaches, either as stand-alone therapies or in combination with current state-of-the-art treatments. These novel approaches should be informed by translational research into the underlying mechanisms of binge-eating. Neurobiological evidence [7] suggests that people affected by BED show difficulties along the spectrum of impulsivity [8, 9], including altered reward processing [10], impaired inhibitory control [11] and emotion regulation capacities [12], which also involves changes in underlying neurocircuit functioning [7]. For instance, the dorsolateral prefrontal cortex (dlPFC) is involved in response inhibition [13], and patients with BED have demonstrated reduced activation in the dlPFC together with impaired response inhibition performance on a behavioural level [14]. This identifies the dlPFC as a potential treatment target in patients with BED, and one approach to influence brain areas such as the dlPFC entails non-invasive brain stimulation (NIBS).

NIBS entails different techniques which allow for the transcranial influence on the excitability of the brain. Therefore, NIBS can be used to influence brain areas involved, for instance, in inhibitory control processes [15]. One common NIBS approach is transcranial direct current stimulation (tDCS), a technique which applies a weak constant current of one or two mA via electrodes to a specific brain area through the scalp [16]. The current alters the membrane potential of the neurons thus increasing or decreasing the probability of neuronal firing. In simplified terms, anodal stimulation increases and cathode tDCS decreases cortical excitability [15–17]. A recent meta-analysis supports that tDCS exerts significant effects on inhibitory control as assessed by the Stop Signal Task (SST) in healthy and in clinical populations [18].

### Existing knowledge

Recently, NIBS has been used to influence eating behaviour and has been probed in the treatment of eating and weight disorders, while most studies have used tDCS as a technique [15, 17, 19]. Evidence in healthy and sub-clinical groups as well as in people affected by obesity suggests that tDCS and other forms of NIBS can reduce (short-term) food cravings [15], however, studies investigating the potential of NIBS in clinical populations are still very scarce and have mostly focused on patients with anorexia nervosa (AN) [15]. There is to the best of our knowledge only one published study which has probed the use of tDCS in a sample of people affected by BED or sub-clinical BED [20]. In this study, 30 individuals with BED received either a verum or sham stimulation of the right dlPFC with 2 mA [20], and the verum stimulation resulted in reduced short-term food craving and urge to binge-eat in male participants only and in overall reduced caloric intake directly after the stimulation. Of note, this study exclusively used tDCS as an intervention and did not pre-define a primary outcome or planned subgroup analyses.

However, it has to be considered, that tDCS itself does not induce neuronal activity like e.g. transcranial magnetic stimulation and its effects therefore critically depend on concurrent brain activity [21, 22]. This property of tDCS thus allows for targeting specific networks and associated cognitive or behavioral functions [23–25]. Therefore, a targeted combination with training has been put forward as a promising approach to support adaptive plasticity underlying the therapeutic effects of tDCS [16, 26, 27]. Therefore, combinations of tDCS and cognitive training approaches are discussed as a promising new treatment approach [16]. Particularly, tDCS administration to the prefrontal cortex during task training has shown some promising effects in patients with depressive disorder [28–30] and schizophrenia [16, 31]. BED is also associated with dysfunctions in prefrontal brain areas [14] and patients with BED have demonstrated impairments in a range of cognitive tasks, predominantly in the domain of inhibitory control [9]. These tasks can also be used in terms of training tools to enhance cognitive control [19].

In line with this recent development in the field of NIBS, there is one ongoing feasibility RCT probing a food-related cognitive bias modification training combined with tDCS in people with BED [32]. This study targets the right dlPFC with anodal stimulation and the left dlPFC with cathodal stimulation with 2 mA [32]. In the cognitive domain, especially if inhibitory control is demanded, the right dlPFC seems to be crucially involved and performance might be improved by anodal tDCS [33]. Furthermore, it could be shown, that food craving could be reduced by anodal tDCS of the right dlPFC [34, 35]. Besides, there are three further related registered trials, two are using a different NIBS approach in patients with BED which is repetitive transcranial magnetic stimulation (rTMS) [36] (NCT04129970), and a further trial is combining tDCS with nutritional counselling (NCT04226794).

Prior to the present randomized controlled pilot trial (RCT), we have conducted two proof-of-concept (POC) studies to assess underlying mechanisms and feasibility of this treatment approach [37, 38]. In the earlier POC study, we piloted the feasibility and acceptability of a food-specific inhibitory control training which is based on principles of the antisaccade paradigm [39] in patients with BED [38]. The training approach proved to be feasible and acceptable, and participants showed an improved performance regarding inhibitory control towards pictures of high-caloric foods over three training sessions [38]. Within the second double-blind, randomised, sham-controlled POC study, we combined this inhibitory control training with tDCS of the right dlPFC in 31 patients with BED, contrasting effects of 1 versus 2 mA stimulation intensity [37]. We found that this approach was again feasible and acceptable [37]. While there was no overall effect of stimulation on performance measures, decreased latencies for successful response inhibition were found under the 2 mA condition [37], rendering this as the more promising dosage for a treatment intervention, also in line with the ongoing trial on tDCS in BED [32].

### Study aims

Based on (a) emerging neurobiological findings on the role of inhibitory control in the pathology of BED, (b) promising results of previous studies targeting inhibitory control and eating-related outcomes using tDCS and cognitive trainings and (c) data from our POC studies [37, 38], we have designed the present pilot clinical RCT.

The primary aim of the ACCElect trial is to pilot the treatment protocol of six sessions of a food-specific inhibitory control training combined with 2 mA of tDCS to the right dlPFC. This intervention will be compared to training in combination with sham stimulation as a control condition. Specific aims comprise: (a) confirmation of the feasibility of a tDCS-enhanced antisaccade training in BED patients; (b) establishing evidence regarding clinical relevant effects of a tDCS-enhanced antisaccade training to increase cognitive control over eating in BED patients and (c) establishing evidence for a sample size calculation for a larger multicenter RCT on the efficacy of tDCS in increasing cognitive control in BED.

The primary clinical endpoint is binge-eating (BE) frequency as core psychopathology of BED [40] in terms of changes in BE episodes four weeks after treatment termination as compared to baseline. Key secondary outcomes of the trial comprise the investigation of changes in overall ED pathology and general psychopathology, changes in inhibitory control capacities and broadly defined impulsivity, changes in quality of life as well as acceptability and satisfaction with the intervention.

## Methods/design

The present study protocol is reported according to the SPIRIT checklist [41].

### Study design and setting

ACCElect is a single centre clinical pilot double-blind RCT with two parallel arms.

Patients are recruited from the outpatient eating disorder service of the Medical University Hospital Tübingen, via study announcements in the media, via email lists of the University Tübingen, and individuals who have previously participated in ED research study at the Department of Psychosomatic Medicine and Psychotherapy and gave written consent to be informed about future studies are also contacted. People who are interested in the study receive verbal and written information material and are screened using a standardized checklist covering inclusion and exclusion criteria. After providing written informed consent, the baseline assessment takes place. After completion of the baseline assessment, patients will be randomized at a 1:1 ratio to one of the two treatment conditions (see below). As outlined in Fig. 1 and Table 1, the outcomes will be measured at baseline (T0), at each training session (T1–T6), at end of treatment (T7) and at two follow-up timepoints, a four-week follow-up (T8) and a 3-months follow-up (T9).

**Fig. 1 Fig1:**
[figure not shown]
Study procedures and assessment points of the ACCElect trial

**Table 1 Tab1:**
[figure not shown]
Schedule of enrolment, interventions, and assessments within the ACCElect trial according to SPIRIT

### Study participants and eligibility criteria

The study population consists of individuals who have a diagnosis of a full-syndrome BED according to DSM-5 [42].

#### Inclusion criteria

Patients eligible for the trial must comply with all of the following at randomization:Age ≥ 18 yearsBMI > 20 kg/m^2^Written informed consent

#### Exclusion criteria

Insufficient knowledge of German languageCurrent pregnancy or lactation periodCurrent or lifetime psychotic disorder, bipolar-I disorder, current substance dependence, current suicidalityPrevious bariatric surgerySevere somatic diseases which influence weight or eating behaviour (e.g. severe diabetes) and are not controlled by stable medicationSevere neurologic diseaseNon-removable metal parts in the area of the head (besides metal parts in teeth)PacemakerCurrent intake of neuroleptics and benzodiazepinesUncorrected impaired vision, ametropia, eye diseases which prevent from executing the task

### Interventions

Eligible patients receive six sessions of a food-related inhibitory control training, and they will be randomly assigned to receive this either in combination with a verum tDCS of the right dlPFC or in combination with a sham stimulation.

#### Psychoeducation

A short psychoeducation (approximately 5–10 min) is provided by a trained psychologist to all participants, covering an overview on BED, as well as mechanisms of the inhibitory control training combined with tDCS stimulation, and the transfer of the training effects to everyday life.

#### Inhibitory control training

The inhibitory control training is based on the principles of the antisaccade paradigm, an established paradigm requiring prefronal brain activation to suppress prepotent oculomotor reactions to a stimulus presented in peripheral vision [43]. Each trial of the antisaccade paradigm starts with a central fixation cross which is succeeded by a stimulus presented slightly left or right from the cross in a peripheral screen position. The participant is asked to look as quickly as possible upon stimulus onset on the other side of the screen, that is, to perform an antisaccade. We have modified the classical paradigm by using food versus control pictures as peripheral stimuli [38, 39, 44], and found that participants with BED generally had more problems to exhibit antisaccades than BMI-matched obese participants without BED and normal-weight controls, and they had more problems looking away from a food picture they had wrongly looked at [39, 44]. Based on this evidence, the basic idea of the food-specific inhibitory control training is to influence eating behaviour via the improvement of antisaccade performance as a measure of impulsivity. During training sessions, BED patients practice the suppression of a prepotent oculomotor response towards a peripheral food stimulus. On a task level, the aim of the training is the reduction of error rates, that is, the reduction of prosaccades towards food stimuli.

As piloted in the POC study [37], study participants are presented with 40 colour pictures depicting high-caloric food items. The participants rate these pictures concerning valence, i.e. how appetizing the depicted food looks, how much they like the food in general and how much they want to eat it now. Afterwards, the 20 individually highest-rated stimuli are chosen for the training. Each picture is presented four times during one block, while presentation location on the screen (left / right) is counterbalanced. We present the stimuli in four blocks, resulting in 320 trials. Each trial starts with a central fixation cross (1250 ms), succeeded by a 200 ms interstimulus interval. Afterwards, the food picture is presented. After each training session, participants receive feedback about the percentage of errors they have committed.

During task performance, the participant’s gaze behaviour is recorded using a IViewX Hi-Speed eye tracking system (SensoMotoric Instruments, 2010) with a sampling rate of 500 Hz and 0.25°–0.5° gaze position accuracy.

Study participants receive six sessions of the training within 14 days, which is three sessions / week. Hunger and mood are assessed at every training session using visual analogue scales.

#### tDCS

Two 5 × 7 cm electrodes connected to a battery-driven, constant-current stimulator (DC-STIMULATOR MC, NeuroConn GmbH, Ilmenau, Germany) will deliver 15 min of transcranial direct current stimulation (tDCS). The electrodes will be prepared with a Ten20 conductive paste (Weaver and Company, Aurora, CO, USA). An unipolar tDCS montage will be used, placing the cathode extracephalic on the left deltoid muscle and the anode over F4 according to the international 10–20 system of electrode placement [45]. By using an unipolar tDCS montage, solely the right dlPFC should be targeted [46]. After a fade-in of 5 s, the verum group will receive 15 min of 2 mA tDCS, whereas the sham group will only receive 43 s of tDCS before the start of the antisaccade task. This is considered as a valid placebo-condition as typical perceived physical sensations (e.g. tingling) usually fade out in the first 30 s of tDCS [47]. By using a 5-digit number, generated by a person not linked to the study, the stimulator will either apply verum or sham stimulation. Thus both experimenter and participant will be blind regarding the allocated condition.

### Patient safety

After each training, side effects of tDCS will be rated on a scale ranging from 1 (“not at all”) to 5 (“very”): Tingling at the electrode, tingling at other parts of the head, fatigue, slight itching, headache, nausea, other. Other potential (severe) adverse events will be documented by the experimenter.

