### Participant timeline

The individual participant timeline is depicted in Fig. 1.

Study duration for each patient comprises 14 weeks. This includes two weeks of training and a post-intervention follow-up period of three months. Table 1 shows the nine assessment time points during the study (T0–T9), while T0 is the baseline assessment, there is an assessment at each training session (T1–T6), a post-intervention assessment (T7) within the two weeks after training termination, a second post-intervention assessment four weeks after training termination (T8) and a three-months follow-up assessment focusing on changes in ED symptoms conducted via telephone (T9).

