### Randomization

Eligible patients will be randomized 1:1 between the verum stimulation and the sham stimulation. Randomization takes place after completion of the baseline assessment (T0) and is performed independently via a code system established by the Institute for Clinical Epidemiology and Applied Biostatistics, Tübingen, Germany (IKEAB). Block randomization with variable block lengths will be used.

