A further challenge applying to the whole rapidly evolving research area is very limited evidence on which cognitive training approach might work best in terms of sustainable and clinically relevant changes in ED pathology. As outlined above, most previous evidence on the combination of NIBS with cognitive tasks stems from healthy convenience samples or subclinical groups [16, 18], and in the ED field, most studies have used stimulation only approaches [15, 17]. There are multiple well-validated and widely used neuropsychological paradigms to assess prefrontal brain functioning in terms of inhibitory control capacities, including the SST and GoNoGo tasks, but also the antisaccade paradigm. A currently ongoing study uses an approach bias modification training in combination with tDCS [32] as this has previously shown promise in patients with EDs. A recent meta-analysis found significant effects of tDCS on inhibitory control as assessed by the SST in healthy and in clinical samples, but not on GoNoGo performance [18]. It is also important to consider that the most widely used tasks also tap on slightly different sub-components of inhibition, for instance, the SST measures the ability to interrupt an already initiated behavior, while the GoNoGo and antisaccade paradigm assess the ability to suppress a prepotent response. These slight differences might have rather significant consequences when translating into clinical outcomes regarding targeted disorder symptoms as well as for the interplay with stimulation effects which are intended to augment the training effects [16]. Additionally, there is also the potential of delayed effects of tDCS on task performance [54], rendering it interesting for future pilot and efficacy trials to include cognitive task performance also within follow-up assessments. We aim to contribute to this evidence with our trial as more research is needed on which performance aspects are best targeted with the training as well as which aspects can be best augmented using tDCS. Therefore, we are also reporting on GoNoGo performance of our trial participants as secondary outcome.

Our main focus of the 12-week follow-up assessment are potential changes in the central clinical outcomes of the trial, while ensuring low attrition by a concise assessment. However, this was on the expense of other variables, and it would, for instance, be also insightful to have QoL data at follow-up.

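### As described, tDCS side effects are scored only after each training, so fatigue, headache and nausea have no pre-stimulation value and complaints arising after session 6 are not systematically elicited

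*Protocol article*

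**What the plan says.** Patient safety sets the rule: "After each training, side effects of tDCS will be rated on a scale ranging from 1" up to 5. The items are "Tingling at the electrode, tingling at other parts of the head, fatigue, slight itching, headache, nausea, other". One further sentence covers everything else: "Other potential (severe) adverse events will be documented by the experimenter". It gives no time limit and no question to be put to the patient.

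The number of ratings follows from the Inhibitory control training section: "Study participants receive six sessions of the training within 14 days, which is three sessions / week". Participant timeline places the later contacts. After the sessions, "there is an assessment at each training session (T1–T6), a post-intervention assessment (T7) within the two weeks after training termination"; then T8 at four weeks after training, and "a three-months follow-up assessment focusing on changes in ED symptoms conducted via telephone (T9").

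The comparison is randomised and blinded: "Eligible patients will be randomized 1:1 between the verum stimulation and the sham stimulation", with participant and experimenter both unaware of the condition (tDCS and Blinding sections). The Discussion names safety among the results meant to inform larger trials.

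**The concern.** A score taken only after stimulation is a level, not a change. Fatigue, headache and nausea are common complaints with many causes, and Concomitant care allows parallel eating-disorder treatment and most psychoactive medication. A patient who arrives tired and leaves tired can score above 1 on an item headed as a side effect of tDCS.

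A score taken as the session ends also cannot register what begins on the way home. Between sessions the next visit gives a chance to mention it. After session 6 no further structured rating is described.

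At stake is how well the pilot describes tolerability for the planned multicentre trial. The primary outcome and the key secondary outcomes are not affected.

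**Working it through.** The plan states no figure on this point, so there is nothing to reproduce. The check is a count of what is described, followed by reasoning about its effect.

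**Count, per patient (visible text)**

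| Occasion | Contact exists | Structured side-effect score described |
|---|---|---|
| Before stimulation, T1–T6 | yes, 6 visits | none |
| After training, T1–T6 | yes, 6 visits | 6 |
| T7 (up to 2 weeks, or 14 days, after training) | yes | none |
| T8 (four weeks) | yes | none |
| T9 (three months, telephone) | yes | none |

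Hunger and mood are already taken at every session on visual analogue scales, so a short form before stimulation fits the visits as they stand.

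**Effect on rates within an arm.** Let p be the share of patients who arrive with an item above 1. If stimulation adds nothing, the post-session rate is still p. The documents give no p. As an assumption, take 20% to 40%. In an arm of about 20 (40 patients, 1:1), 0.20 × 20 = 4 to 0.40 × 20 = 8 patients would be listed with a side effect that they already had.

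**Effect on the contrast, mean scores.** Write post = pre + d, with d the change during the session. Randomisation makes the expected pre value equal in both arms, so the expected verum-minus-sham difference in post scores equals the difference in d. It is not biased, apart from a ceiling at 5. The pre value still contributes to the variance of each post score; that is the added noise.

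**Effect on the contrast, dichotomised scores.** If items were reported as present or absent (above 1 or not), there would also be dilution. With an assumed independent 20% chance that verum causes the item, and none under sham:

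- p = 20%: verum 0.20 + 0.20 × 0.80 = 36%, sham 20%, difference 16 points.
- p = 40%: verum 0.40 + 0.20 × 0.60 = 52%, sham 40%, difference 12 points.

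The assumed excess of 20 points would appear as 12 to 16. This is an illustration only: the article does not say that the items will be dichotomised.

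**Late onset.** A complaint that begins after a session and has gone by the next one receives no score unless the form's recall window covers it; no window is stated. After session 6 there is no next session. The documents contain nothing from which the share of late complaints could be estimated, so no figure is given.

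**The case against.** The strongest reply is that the article says when a rating is done, without saying that none is done at any other time. It condenses a fuller protocol, Table 1 is not visible, and the recall window, a pre-session form and the adverse-event collection period are details that often sit in such documents. This stands as a limit: the absence of further ratings is read from the visible text and is not established. What the article does fix is the timing of the only structured safety instrument that it describes, and that timing can be assessed.

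Four stronger readings are tempting, and the documents do not support them.

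- *Later complaints are missed.* Other adverse events are to be documented with no stated end, the checklist has an open item, and patients are seen or called again at every later time point. Late complaints may be recorded; they are simply not asked for in a structured way.
- *Existing complaints bias the comparison with sham.* They are balanced in expectation by blinded randomisation. What suffers is the rate within each arm and the precision of the contrast. The form may also ask patients to rate only what they attribute to stimulation, which would reduce the problem to the extent that they can tell.
- *The protocol concedes delayed side effects.* The Discussion says "there is also the potential of delayed effects of tDCS on task performance", which concerns cognitive performance and says nothing about headache or fatigue.
- *T9 excludes safety.* The call focuses on eating-disorder symptoms, which does not limit it to them.

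It is also fair that safety is not among the specific aims or key secondary outcomes in Study aims, and that recruitment is under way, so a new form would split the sample between two versions. Both hold, and they keep this a minor point.

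**Conclusion.** The point holds as a cheap improvement to the measurement schedule. It is not an error or a contradiction in the plan. As described, each patient yields six post-session scores, no pre-stimulation score and no structured score after T6, with up to 14 days before the next contact.

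Two consequences follow. Rates of fatigue, headache and nausea within an arm will include existing complaints and cannot be read as rates caused by tDCS, and the same complaints add noise to the verum-sham contrast. Complaints that begin after the patient leaves, especially after session 6, depend on being volunteered.

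The size of either effect cannot be derived from the documents; the percentages in the working are assumptions. The conclusion also assumes that neither Table 1 nor the study forms already contain further ratings. If they do, one clarifying sentence in Patient safety is enough.

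**What to change.** Unless Table 1 or the forms already provide for it:

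- Give the same short checklist before stimulation at T1–T6. From T2 on, ask in addition about complaints since the last session. Keep the rating after training.
- Repeat the interval version at T7.
- Ask one open adverse-event question at T8 and at the T9 call.
- Report the post-minus-pre change and the between-session onsets by arm.
- State in Patient safety the recall window of the rating and the last visit at which adverse events are collected.

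The cost is about 1–2 minutes per existing contact, with no new visits or staff and slightly more burden for patients. Because recruitment is running, patients already enrolled will have the old form. The report should give the number on each version and restrict the change scores to those with a pre-stimulation value. Values not taken before stimulation cannot be recovered later, so the gain is limited to patients still to be treated.
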